## Methods

### Trial design

The design of this cost-effectiveness study will be described following the CONSORT statement [13]. The study is a supplement to an MST-effectiveness study [14], which concerns a randomized controlled trial (RCT) with a follow-up measurement after 6 months. Participants will be randomly assigned to one of the two groups: MST or Care-As-Usual (CAU). Data will be collected using a standardized self-report questionnaire in a face-to-face situation before treatment (T1), immediately after treatment (T2) and at follow up (T3; 6 months after treatment) among adolescents, parents/primary carers and therapists. Adolescents and their parents will both receive €10 for filling out the questionnaire. The Medical Ethics Committee of Utrecht University approved the study design, protocols, procedures and informed consent. Participation is voluntary and all participants are asked to provide written informed consent at T1.

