### Recruitment

Participants will be recruited via three MST institutions spread over the Netherlands. The recruitment per organization will differ because of differences in the setting in which MST will be delivered. One MST organization is located in the North of the Netherlands; the other two locations are in the West of the Netherlands.

In *the North of the Netherlands*, the study population will consist of adolescents referred by family guardians of the Youth Care Office to the youth care program called “Do What Works”. This program consists of maximum six weeks secure residential care, followed by MST (Intervention) or FFT (Functional Family Therapy; Care-As-Usual). After the residential period, adolescents will be randomized to MST or to Care-As-Usual. At the same time, adolescents and their parents will be informed about the MST-effectiveness study and they will be asked for their informed consent. Upon mutual consent of the adolescent and the parents, a first appointment will be made before the start of MST or Care-As-Usual, in order to obtain written informed consent and to administer the first questionnaire.

The recruitment in *the Western part of the Netherlands* will be conducted via referring agencies such as Child Protection Council, juvenile judges, Bureaus Youth Care and local referral institutions. The referrers will inform the potential eligible juveniles and their families that a study will be conducted to investigate the effectiveness of youth care. If the families meet the inclusion criteria for MST according to the MST supervisors of the participating institutions, research procedures will be explained to the juveniles and their families, and their informed consent to participate in the study will be obtained by researchers.

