### Randomization

Immediately after referral (Western part of the Netherlands) or after the residential period (Northern part of the Netherlands), participants will be randomized to MST or CAU with the use of a computerized randomization program. This program will execute the randomization separately for each site. The ratio of randomization between MST and CAU will be 1:1.

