### Strengths and limitations

This study will contribute to the extension of scientific knowledge about economic evaluation in the field of child and youth care. This concerns the evaluation of the actual balance between costs and effects in a field of care where this has hardly ever been explored before, i.e. with very limited sources to derive costs of other outcome valuations from. The study will be conducted as part of a randomized controlled trial. By using such a design, it can be assumed that any confounding variables are cancelled out.

Furthermore, the study will be conducted as a multicentre trial. This will increase the generalizability of the study because this will lead to a large number of participants, different geographic locations and the ability to compare results among organizations. We will obtain both direct and indirect costs across the entire field of youth care. We will also include quality of life measures. To increase inclusion and prevent loss to follow up, all adolescents and parents will receive assistance in administering the questionnaires. Finally, most outcome variables will be assessed via two informants. Multi-informant assessment is recommended as a way to obtain a more complete picture of the adolescent than reliance on self- or parent-report alone [16].

Despite the strengths and innovative aspects of this cost-effectiveness study, there are some issues that our study is unable to take into account. First, follow-up is limited to a period of six months. To determine long-term effects of the intervention, there should be follow-up after a couple of years to assess the effects and costs when the adolescent is older. Second, it is to be expected that we will be dealing with a ‘difficult-to-reach”-population.

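### Randomisation comes before written consent and the T1 questionnaire (explicit in the North, implied in the West), and nothing says the allocation is withheld until both are complete

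*Protocol article*

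**What the plan says.** These sections of the protocol article bear on the order of events and its use in the analysis.

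- **Recruitment, North:** "After the residential period, adolescents will be randomized to MST or to Care-As-Usual. At the same time, adolescents and their parents will be informed". The information concerns the study, and they are asked to take part. If they agree, "a first appointment will be made before the start of MST or Care-As-Usual, in order to obtain written informed consent and to administer the first" (the T1 questionnaire).
- **Recruitment, West:** "If the families meet the inclusion criteria for MST according to the MST supervisors of the participating institutions, research procedures will be explained", and researchers then obtain consent. This paragraph does not say where randomisation falls.
- **Randomization:** "Immediately after referral (Western part of the Netherlands) or after the residential period (Northern part of the Netherlands), participants will be randomized", in a 1:1 ratio, by a computer program run separately for each site.
- **Trial design:** "all participants are asked to provide written informed consent at T1". T1 is defined as before treatment, not as before randomisation.
- **Statistical analysis:** the arms are compared on pre-post difference scores, and the ICERs are computed on complete cost-effect pairs.
- **Strengths and limitations:** "By using such a design, it can be assumed that any confounding variables are cancelled out".

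**The concern.** Randomisation balances the set of people who are randomised. If families can still decline after that point, the set that supplies data is chosen after allocation, and the choice may differ by arm. A family that declines gives no questionnaires, so it is absent from the difference scores and from the complete cost-effect pairs.

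The second route is the baseline. The CBCL and YSR outcomes are reports by parents and adolescents, collected face to face. If T1 is completed after allocation and the family or the data collector knows the arm, expectations can colour the answers. Because the arms are compared on change from T1, any such shift goes straight into the treatment effect.

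Both routes weaken the article's argument that randomisation deals with confounding. A larger sample cures neither.

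**Working it through.** **Step 1. The order of events, region by region.**

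| Event | North | West |
|---|---|---|
| Eligibility check | time not stated | after referral, by MST supervisors (Recruitment) |
| Randomisation | after the residential period (Recruitment and Randomization agree) | directly after referral (Randomization); not placed in Recruitment |
| Study explained, consent asked | at the same time as randomisation | after the eligibility check (Recruitment) |
| Written consent and T1 | later appointment, before treatment | written consent at T1 (Trial design) |
| Allocation withheld until T1 is complete? | not stated | not stated |

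In the North, randomisation before written consent and T1 is explicit. In the West it follows from reading Randomization with Trial design. Read literally, the western timing in Randomization also comes before the eligibility judgement and consent described under Recruitment, so the two sections need reconciling for that region.

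**Step 2. How T1 enters the effect.** The between-arm estimate is mean(T2 − T1) in MST minus mean(T2 − T1) in CAU. If knowledge of allocation shifts mean T1 in one arm by δ and leaves T2 unchanged, the estimate moves by δ in absolute value. The documents give nothing from which to size δ.

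**Step 3. The yardstick.** The plan gives no figure for this bias. Its planned effect is 0.5 SD (Sample size: alpha .05, power .80, medium effect). That input reproduces the stated 64 per group: 2 × (1.960 + 0.842)² / 0.5² = 62.8, so 63 by the normal approximation and 64 by the t-test.

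**Step 4. Size of selective refusal, for illustration.** The documents give no consent rates, so all inputs here are assumptions: 100 randomised per arm, no true effect, unit SD, consent proportion p in each arm, and correlation ρ between willingness to consent and the analysed score. Since the analysis uses change, ρ refers to change; stable differences in level between families who stay and families who leave cancel out.

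Under a latent-normal selection model the mean shift among those who consent is ρ × φ(z)/p, where z is the normal quantile at 1 − p. The bias is the difference between arms:

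bias = ρ × [φ(z_CAU)/p_CAU − φ(z_MST)/p_MST]

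- p = 0.90: φ/p = 0.1755/0.90 = 0.195
- p = 0.80: φ/p = 0.2800/0.80 = 0.350
- p = 0.70: φ/p = 0.3477/0.70 = 0.497

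Type I error uses SE = √(1/(100 p_MST) + 1/(100 p_CAU)) and a two-sided 5% test.

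| Consent MST / CAU | ρ | Bias (SD) | Type I error |
|---|---|---|---|
| 90% / 80% | 0.1 | 0.155 × 0.1 = 0.015 | 5.1% |
| 90% / 80% | 0.5 | 0.155 × 0.5 = 0.077 | 8.0% |
| 90% / 70% | 0.1 | 0.302 × 0.1 = 0.030 | 5.4% |
| 90% / 70% | 0.5 | 0.302 × 0.5 = 0.151 | 15.7% |
| equal, same ρ in both arms | any | 0 | 5% |

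Against 0.5 SD, the non-zero rows run from 0.015/0.5 = 3% to 0.151/0.5 = 30% of the planned effect. The bias formula contains no sample size, so recruiting more families does not shrink it.

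**The case against.** The strongest reply is that both mechanisms need the arm to be known, and no section says that families know their allocation when they agree, sign or complete T1. In the North the consent request coincides with randomisation, and T1 precedes treatment. The article also condenses a design that supplements a separate effectiveness study, where the timing of disclosure may be described. This stands as a limit: bias is a risk left open, not something shown. It does not remove the point, because the article itself gives an order in which refusal and T1 come after allocation and states no safeguard.

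A reader might go further and infer that families everywhere are randomised before eligibility is established, and that MST supervisors can exclude families knowing their arm. The documents do not support this. For the North the time of the eligibility check is not given, and the supervisors' judgement appears only in the western paragraph. For the West the inference depends on a strictly literal reading of the Randomization section; the participants it refers to could be families already accepted.

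A reader might also infer that Recruitment and Randomization contradict each other in general. For the North they agree. For the West the conflict is implied, since Recruitment does not place randomisation there.

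Finally, recidivism taken from the judicial database is not exposed to coloured T1 reporting. That is correct, and it narrows the second route to the reported outcomes.

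**Conclusion.** The point holds in a limited form. Written consent and T1 follow randomisation, explicitly in the North and by implication in the West, and nothing says the allocation is withheld until they are complete. Refusal can therefore vary by arm, and T1 reports that feed the difference scores may be influenced by allocation. The assurance about confounding goes further than this procedure supports.

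The size is unknown. Bias from selective refusal is zero if consent and selection are equal across arms, and roughly 0.015 to 0.15 SD under the consent rates and correlations assumed above. None of those inputs comes from the documents. The effect on T1 reporting cannot be sized from them at all. The case for changing the procedure is that analysis cannot fully repair either problem afterwards, while prevention is cheap.

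**What to change.** 1. In each region, complete the eligibility check, written consent and T1 before randomising. The regions may keep different recruitment routes. If randomisation has to come first somewhere, keep the allocation undisclosed to families and data collectors until consent and T1 are complete, and say so.
2. Correct the northern paragraph of Recruitment, and for the West reconcile Recruitment with Randomization, so that each region has one stated sequence. The Trial design sentence placing written consent at T1 can stand.
3. Report by arm the numbers randomised, refused and excluded. For families already randomised who declined, such counts are what can clearly be supplied, since they provide no questionnaire outcomes.
4. Qualify the statement under Strengths and limitations: randomisation protects the comparison of all who were randomised, and entry after allocation can weaken that protection.

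The cost is a procedural amendment and a short delay before allocation is released.

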### Participants

Participants eligible for this study are adolescents (and their families) between 12 and 18 years old who show serious, violent, and chronic antisocial behaviour. Exclusion criteria are an IQ below 70, acute psychiatric problems that place adolescents and their family at risk for out-of-home placement, and dominant sexual problems. Adolescents may be court-ordered or referred by primary health care, social workers or self-referred.

### Interventions

**MST**. Multisystemic Therapy (MST) is an intensive, short-term, home- and community- based intervention program for families of youth with severe psychosocial and behavioural problems. It is based on the social ecological theory of Bronfenbrenner [15] and on models of the cause of delinquency [16]. MST is designed to address complex psychosocial problems and provides an alternative treatment for out-of-home placement of children and youth. It uses the various systems in which the adolescent is embedded: family, peer group, school and neighbourhood. In consultation with the members of the family, the therapist identifies a set of treatment goals and assigns the tasks required to accomplish these goals. MST lasts 4 to 6 months and takes the individual needs of the client into account. Therapists are available 7 days a week, 24 hours a day. Each team includes 3–5 therapists who have a caseload of 3–5 clients each.

**CAU**. Care-As-Usual consists of treatments that are already available for adolescents with severe psychosocial and behavioural problems: juvenile justice services, child welfare services, individual adolescent counselling and home-based social services (for instance, parental counselling). Also included and variably implemented across regions are recently developed, evidence-based services such as Functional Family Therapy (FFT) [17] and Multi-Dimensional Family Therapy (MDFT) [18].

### Randomization

Immediately after referral (Western part of the Netherlands) or after the residential period (Northern part of the Netherlands), participants will be randomized to MST or CAU with the use of a computerized randomization program. This program will execute the randomization separately for each site. The ratio of randomization between MST and CAU will be 1:1.

### Outcome measures

In cost-effectiveness studies, costs are linked to treatment or clinical outcomes. All outcomes will be assessed at all three measurement moments.

#### Primary outcomes

Primary outcomes of this study include: recidivism and the frequency and seriousness of antisocial behaviour and other types of problems (internalizing problems, substance use). *Recidivism* will be assessed with data of the Research and Policy Database for Judicial Documentation. With this data we will assess the number of arrests, type and severity of offence of adolescents re-offending during the research period.

*Prevalence and seriousness of antisocial behaviour* will be assessed via different informants and instruments. First, parents and adolescents are asked to fill in the 33 items of the Delinquent Behaviour scale and the Aggressive Behaviour scale of the Child Behaviour Checklist (CBCL: 33 items) [19] and the Youth Self Report (YSR: 30 items) [20,21] respectively. For each item, the child’s behaviour has to be rated on a three-point scale, ranging from 0 (never) to 2 (often).

Additionally, adolescents will fill in two subscales of the Self-Report Delinquency scale (SRD) were used to assess self-report delinquency [22]. Adolescents will be asked to indicate on a list of potential delinquent behaviours whether they engaged in the described behaviours during the past 6 months (‘yes’ or ‘no’). The SRD ‘Violent offending’ (5 items) and ‘Property offences’ (10 items) scales will be used.

*Other types of problems* of the adolescent firstly comprise anxiety/depression, withdrawal and somatic complaints. These items will be measured with 25 items of the Youth Self Report [20,21].

In addition substance use (use of alcohol, soft and hard drugs) will be measured with several questions from a Dutch questionnaire used in the study Youth and risky behaviour [23].

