**Methods:**

The cost-effectiveness of MST will be assessed through a Randomised Controlled Trial. Primary outcomes aggressive and delinquent behaviour will be assessed with the parent-reported CBCL and adolescent-reported YSR. Health care utilisation, production loss, and quality of life are recorded using the self-report 'Trimbos and iMTA questionnaire on Costs associated with Psychiatric illness' (TiC-P), and with the MOS Short-Form General Health Survey (SF-20) and EuroQol -5D (EQ-5D), respectively. The study aims to enrol 100 clients in both conditions (MST and CAU). Data will be obtained before treatment (T1), immediately after treatment (T2; 5 months after T1) and at follow up (T3; 6 months after the end of the treatment) from a variety of sources, i.e. clients, parents/primary carers, professionals and police records.

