### Sample size

Sample size will be based on testing differences in outcomes between MST and CAU, at .80 power, an alpha of .05 and a medium effect size [34]. This leads to 64 participants per group. It should be noted that the power to detect a difference in costs and/or other outcomes is extremely difficult to assess a priori. Since this is a first attempt to perform a cost-effectiveness study in this area and no pilot data are available (allowing an assessment of variability) we cannot present a formal power calculation. However, to determine a clinically relevant effect size of 0.5 with a power of 80% at an alpha of 0.05, we will need 81 in each treatment arm, making 2 × 100 a probably safe sample size [35].

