### Statistical analysis

First, descriptive statistics will be performed to describe the demographic characteristics of the study population.

Second, primary measures of effect will be analysed using within group comparisons (pre-post treatment) and between group comparisons. The latter one will use difference scores (pre-post intervention) after which the treatment effects of the two treatment conditions will be compared. Statistical testing will be done using either the paired t-test or the Wilcoxon signed-rank test for comparisons within the treatment groups and the unpaired t-test or the Mann–Whitney U test for comparisons between the treatment groups.

Third we will describe the mean costs per respondent in both treatment groups. Differences in costs between the intervention group and the control group will presented based on the trial data, and 95% confidence intervals will computed based on bootstrap re-sampling with 5000 replications of the trial data. Separate estimates will be made for different cost categories. For the cost-effectiveness analysis, mean annual societal costs will be linked to the primary measure of effect (Aggressive behaviour and Delinquent behaviour). A cost utility analysis will link the EQ-5d based utilities to the cost.

Fourth, point estimates for the incremental cost-effectiveness and cost utility ratio (ICER) will be computed on complete cost-effect pairs by dividing the incremental societal costs by the incremental effects at 12 months. Uncertainty around the ICERs will be estimated using bootstrapping, generating 5000 replications of the original dataset. A cost-effectiveness acceptability curve (CEAC) will be generated to represent the probability that MST is cost-effective compared to usual care over a range of thresholds [26,36].

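### The Methods list of primary outcomes is wider than the one in the abstract and cost-effectiveness analysis, and no single score is named as the ICER effect measure

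*Protocol article*

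**What the plan says.** The protocol article describes the primary outcomes in three places.

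- **Abstract, Methods:** "Primary outcomes aggressive and delinquent behaviour will be assessed with the parent-reported CBCL and adolescent-reported YSR". Two constructs and two informants give four scale scores.
- **Methods, Primary outcomes, opening sentence:** "Primary outcomes of this study include: recidivism and the frequency and seriousness of antisocial behaviour and other types of problems (internalizing problems, substance use". The text below this sentence adds judicial-record recidivism, two self-report delinquency (SRD) scales, internalizing problems from the YSR, and alcohol and drug use. All of these stand under the primary heading.
- **Methods, Statistical analysis:** the primary measures, in the plural, are tested within and between groups on pre-post differences. For the cost-effectiveness analysis, annual costs are then "linked to the primary measure of effect (Aggressive behaviour and Delinquent behaviour"). Here the measure is singular, covers two constructs and has no informant attached. The ICER uses effects at 12 months.

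The Sample size section plans for a comparison "at .80 power, an alpha of .05 and a medium effect size" and concludes: "This leads to 64 participants per group". It then gives a second figure for an effect size of 0.5 with the same power and alpha: "we will need 81 in each treatment arm, making 2 × 100 a probably safe sample size".

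**The concern.** The abstract and the cost-effectiveness text agree on the constructs; the Primary outcomes section does not agree with them. A reader of the final report could not tell from this article whether a difference in recidivism, SRD score, internalizing problems or substance use was a planned primary result or a secondary one.

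The second gap concerns the study's headline result. An ICER needs one effect in its denominator. Aggressive and delinquent behaviour, each reported by parent and adolescent, could be used as four separate denominators, as sums within informant, or in some other combination. The article does not choose. Parent and adolescent reports may differ, so the ratio and the acceptability curve could depend on a choice made after the data are seen.

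The sample size was worked out as for one comparison. If several scores carry primary status, either the error rate or the power differs from what that section implies.

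**Working it through.** **1. Side-by-side reading**

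| Outcome | Abstract | Primary outcomes | Cost-effectiveness text |
|---|---|---|---|
| Aggressive and delinquent behaviour | primary, CBCL and YSR | primary, CBCL and YSR | effect measure, informant not named |
| Recidivism | not named | primary, listed first | not named |
| SRD scales | not named | primary | not named |
| Internalizing problems | not named | primary | not named |
| Substance use | not named | primary | not named |

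The conflict is between the middle column and the outer two. The missing informant is a separate gap in the last column.

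**2. Reproducing the planned size**

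Inputs from Sample size and Randomization: standardised difference d = 0.5, power 0.80, alpha 0.05, and "The ratio of randomization between MST and CAU will be 1:1". Two-sided testing is assumed, because the article does not state sidedness.

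- Normal approximation: n = 2(1.960 + 0.842)² / 0.5² = 2 × 7.85 / 0.25 ≈ 62.8, so 63 per arm.
- Exact two-sample t-test: 63.8, so 64 per arm.

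The stated 64 is therefore the number for one comparison at .05. The second figure, 81, does not follow from the same inputs (power at 81 per arm is 88.5%); that is a separate matter.

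**3. Error rate if the abstract's four scores are each tested at .05**

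That each is tested at .05 is an assumption.

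- Independent tests: 1 − 0.95⁴ = 0.185.
- Equally correlated normal test statistics, by simulation: 0.174 at correlation 0.3, 0.156 at 0.5, 0.132 at 0.7.

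The article gives no correlations, so 0.3 to 0.7 is an assumed range.

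**4. Upper bound for the Primary outcomes list**

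Counting every item that could be tested separately gives CBCL 2 + YSR 2 + SRD 2 + recidivism 3 + internalizing 3 + substance use 3 = 15. Then 1 − 0.95¹⁵ = 0.537 if independent, and 0.46 to 0.26 at correlations 0.3 to 0.7. The article does not state this count, so these figures are only a ceiling.

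**5. Power if four scores stay primary**

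The first Holm step is at 0.05 / 4 = 0.0125. With d = 0.5 and the exact t-test:

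- 80% power needs 90.8, so 91 evaluable per arm.
- Power is 62% at 64 per arm and 84% at 100 per arm with no loss.
- From 100 randomised per arm, 91 evaluable allows a loss of 9 / 100 = 9%.
- At an assumed 20% loss, 80 per arm remain and power is about 74%.

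**The case against.** The case against making much of this is strong on several counts.

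- **Constructs.** The abstract and the analysis section agree on the constructs. For the cost-effectiveness question, the analysis section does narrow the longer list. This stands: recidivism is not dropped without trace, and the conflict lies with one section.
- **Error rate.** A reader might infer that the trial can claim success on any of about 15 outcomes, each at .05. The article does not say so. The value .05 appears only under Sample size, no success rule is written, and a multiplicity procedure may sit in an analysis plan that is not shown. Its absence here is not itself a fault.
- **Fifteen tests.** Offence type is a category that does not suit the t-test or Mann–Whitney test on differences, and neither substance use nor internalizing problems is said to give three tested scores. It would also be wrong to say that a chance primary finding is likely: only 15 independent tests pass 50%, and independence is implausible for overlapping behaviour scales in the same adolescents.
- **Time points.** A reader might add a second round of tests at follow-up. The between-group test is defined on pre-post differences, and no hypothesis test at T3 is specified.
- **ICERs.** Four ICERs are possible but not stated, and a combined score is not excluded. ICERs and acceptability curves are estimates, so a familywise error rate does not measure the risk to the cost-effectiveness conclusion.

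These points limit the size of the concern. They do not remove the disagreement between the sections or supply the missing denominator.

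**Conclusion.** The concern holds in a limited form. The Primary outcomes section gives primary status to recidivism, SRD delinquency, internalizing problems and substance use; the abstract and the cost-effectiveness text do not. The cost-effectiveness text also leaves open whether parent report, adolescent report or a combination is the ICER effect measure. Both defects are in the printed text and do not depend on what an analysis plan might add about multiplicity. As written, they leave the claimable primary results and the ICER denominator open to choice after the data are seen.

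The error-rate figure is conditional. Four scores each tested at .05 would give 18.5% if independent, or about 13–17% over the assumed correlations. The longer list would give more, but the article does not fix how many measures are tested, so no single figure applies. The documents do not support saying that the trial will be judged positive on any one outcome.

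**What to change.** Use the same primary definition in the abstract, Primary outcomes and Statistical analysis. Aggressive and delinquent behaviour is the natural choice, because two of the three places already use it. Label recidivism, SRD, internalizing problems and substance use as secondary.

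Name in advance one score and one time point as the effect measure for the base-case ICER, consistent with the 12-month ICER already planned, and report the other informant as a sensitivity analysis. The parent CBCL is one option; nothing in the article requires it over the YSR or a combination, and the article presents multi-informant assessment as a strength. Because the between-group test is on pre-post differences, state whether that test and the ICER are meant to use the same time point.

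If all four scores are to stay primary, apply Holm across them and restate the power. The requirement of 91 evaluable per arm leaves little room, given that the authors expect a population that is hard to reach and compute ICERs on complete pairs.

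The change is to wording and needs no new data. Its cost is that fewer outcomes can be claimed as primary.
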